### Expected results

We expect to find several motor, sensory, electroencephalogical, and cognitive prodromal markers for early detection of dementia and its pre-stages. Our assumptions are based on a current literature overview including international and national study results [18, 19, 23, 113].

### Trial registration

The trial was retrospectively registered at German Clinical Trials Register (DRKS) with registration number DRKS00013167 (https://www.drks.de/drks_web/navigate.do?navigationId=trial.HTML&TRIAL_ID=DRKS00013167; http://apps.who.int/trialsearch/Trial2.aspx?TrialID=DRKS00013167; Date of registration 11 April 2018).

## Conclusion

This study aims to detect possible motor, sensory, electroencephalogical, and cognitive predictors to develop a screening tool for dementia and its pre-stages in older adults, aged ≥80 years. Thus, affected individuals could receive optimal health care at an earlier stage to better-maintain their health resources. Nevertheless, some study limitation have to be mentioned. First, cognitive decline will be determined based on the results of cognitive instruments (MoCA and CERAD-Plus) and not based on imaging or cerebrospinal fluid measures [9]. Next, participation in the study is voluntary and the participants have to come to the labs by themselves. This may lead to an inadvertent recruitment of persons with higher cognitive or physical performance levels. Due to the funding period of 3 years and the different time points of study recruitment, it is not possible to observe cognitive decline of the participants over an extended period. Despite of the use of reliable and valid instruments to detect predictors for an early screening tool for cognitive decline, practice effects cannot be excluded completely. In spite of these limitations, a longitudinal design clearly outweighs a cross-sectional one. The present study is one of few studies [53, 54] investigating cognitive, motor, sensory, and neurophysiological markers in combination to develop a multi-dimensional instrument to predict cognitive decline or dementia.

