Furthermore, other motor changes might be used for predicting dementia, e.g., dynamic balance control, finger dexterity, and cutaneous sensitivity*.* Many anatomical structures (e.g., the brainstem, spinal cord, or the primary somatosensory cortex [25–29]), associated with processing cutaneous sensations, are negatively affected in dementia, early dementia, or its precursor MCI. To date, however, there are only few studies which investigate cutaneous sensitivity in MCI patients or dementia diseases [30]. Cutaneous sensitivity is essential for motor performance [31], gait [32], and balance [33]. Quasi-static balance [34] has already been identified as a prodromal marker of dementia [18], whereas dynamic balance with unexpected perturbations has not yet been explored in patients with MCI. Changes in finger dexterity could be predictors for the development of dementia [35], independently from age-related changes [36]. For instance, Rabinowitz and Larner [37] revealed that patients with MCI or dementia show an increase in duration and variability of the finger-touch phase during finger tapping compared to cognitively healthy OA.

Furthermore, neurophysiological techniques, including electroencephalography (EEG), enable detection of functional changes in brain activity at an early stage of dementia [38, 39]. Resting state EEG reveals differences between persons with dementia or pre-clinical dementia and healthy OA [38, 39]. The limited number of longitudinal studies have identified the mean frequency of the total spectrum [40], relative beta power [41], relative alpha power [41–44], relative theta power [40, 42, 45], coherence across all frequencies [40], and coherence in the delta band [46] as possible predictors of cognitive decline. Unfortunately, there is not yet a clear consensus about which parameters best predict dementia or how to translate these findings into cut-offs for individual diagnosis.

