## Methods

### Study aims

The following main research question investigated in this study is:

Which cognitive, sensory, motor, and neurophysiological variables are predictors of the transition from subjective cognitive impairment or MCI to dementia in comparison to age-matched healthy OA?

The objective of the SENDA study is to develop a multi-dimensional sensor-based instrument based on the stated variables or their combination to detect cognitive decline or dementia in OA.

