### Sample size

The sample size calculation was based on the outcome cognitive decline. Based on literature [47, 51] small to moderate effect sizes are expected. Statistical power analysis using G*Power (Version 3.1.9.4, Franz Faul, University of Kiel, Germany) showed that 200 participants are required for analysis with α = .05 and power = .80. Expecting a 20% dropout rate during the study period, 240 participants will be included.

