### Statistical analyses

A multiple regression model (with e. g. ordinary least squares technique) is used to detect several predictors or mediators of cognitive decline. To identify the most parsimonious model, and with it the final predictors, we analyze the corresponding coefficients of determination and consider the multiple comparisons problem providing a proper method to counteract it. Additionally, we propose an alternative classification taking hand of the k-nearest neighbors algorithm. Furthermore, we analyze changes in motor, sensory, electroencephalogical, and cognitive parameters over time in all three groups using mixed-effects models to explain the correlations in repeated measures in the same subject. Hazard ratios of progressing to dementia for participants with cognitive, motor, sensory, and neurophysiological decline are obtained in the classical way using the Cox semi-parametric proportional hazard model. Several variables are included as potential confounders, such as sex, age, education, comorbidities, psychological status, and social support. The most appropriate procedure for handling missing data will be selected after inspecting the amount and pattern of missing data.

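### The aim is a screening instrument, but the stated selection criterion (R-squared) and reported measure (hazard ratios) do not measure how well individuals are classified, and the k-nearest-neighbours alternative has no stated accuracy measure

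*Protocol article*

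**What the plan says.** Study aims gives the objective as "to develop a multi-dimensional sensor-based instrument based on the stated variables or their combination to detect cognitive decline or dementia in OA". The Conclusion says the predictors are sought in order to "develop a screening tool for dementia and its pre-stages in older adults", from which affected people should receive care earlier. The Background, reviewing EEG markers, names as unresolved which parameters predict best and "how to translate these findings into cut-offs for individual diagnosis". Use in individuals is therefore part of the study's own rationale.

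Cognitive status defines decline as a move from one status category to a worse one, so the outcome to be detected is categorical.

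Statistical analyses contains three elements that bear on the instrument:

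- A multiple regression, with ordinary least squares as the example. To reach the most parsimonious model and its final predictors, "we analyze the corresponding coefficients of determination and consider the multiple comparisons problem".
- A Cox model, giving "Hazard ratios of progressing to dementia for participants with cognitive, motor, sensory, and neurophysiological decline".
- A classifier: "we propose an alternative classification taking hand of the k-nearest neighbors algorithm". No performance measure is attached to it.

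Sample size asks for 200 analysable participants at alpha 0.05 and power 0.80, on the basis that "small to moderate effect sizes are expected".

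**The concern.** A screening instrument is judged by its errors: the share of future decliners it flags, the share of non-decliners it leaves alone, and the probability that a flagged person declines. R-squared is explained variance, and a hazard ratio is a relative rate. Both describe association, and neither gives these error rates. A marker can be a clear predictor at group level and still miss most decliners at any usable cut-off.

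The stated criterion has a second weakness. Many cognitive, EEG, gait, balance, fine-motor and sensory variables compete for a place in the model, with about 200 people. The R-squared of the chosen set, computed on the same people, will flatter that set. The planned attention to multiple comparisons addresses false-positive tests, not this optimism.

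At stake is whether the final claim follows from the analysis. If the results are a list of predictors, an R-squared and some hazard ratios, the question of individual cut-offs raised in the Background stays unanswered.

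**Working it through.** **1. Aim against measure**

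| Element of the plan | What it yields | Error rates of a screening decision? |
|---|---|---|
| Regression, final predictors by R-squared | Explained variance of the outcome | No |
| Cox model | Relative rate of progression to dementia | No |
| k-nearest neighbours | A class for each person | Could, but no accuracy measure is stated |

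**2. What effect does N = 200 imply?**

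The figure of 200 cannot be reproduced uniquely, because effect metric, test and number of predictors are not given. Solving backwards (two-sided alpha 0.05, power 0.80), these all fit:

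- correlation r = 0.197: N = 200
- one regression coefficient, f² = 0.04: N = 199
- two equal groups, d = 0.40: N = 198
- joint test of 10 predictors, f² = 0.085: N = 201
- three-group ANOVA, f = 0.22: N = 203

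Each lies between a conventional small and a conventional moderate effect.

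**3. From detectable effect to discrimination**

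Assumptions, none of them in the article: a binormal model with equal variances and a share p of decliners between 10% and 50%.

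- R² = f²/(1 + f²)
- d = √[R²/((1 − R²) p(1 − p))] = √[f²/(p(1 − p))]
- AUC = Φ(d/√2)
- sensitivity at 80% specificity = 1 − Φ(0.8416 − d)

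Single predictor, f² = 0.0396 (R² = 0.038, r = 0.195):

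- p = 0.50: d = √(0.0396/0.25) = 0.40; AUC = 0.61; sensitivity = 1 − Φ(0.44) = 33%
- p = 0.10: d = √(0.0396/0.09) = 0.66; AUC = 0.68; sensitivity = 1 − Φ(0.18) = 43%

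At p = 0.15, d = √(0.0396/0.1275) = 0.56, AUC is 0.65 and sensitivity 39%. PPV = 0.388 × 0.15/(0.388 × 0.15 + 0.20 × 0.85) = 0.0582/0.2282 = 25.5%, against a base rate of 15%.

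Joint test of several predictors at N = 200:

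| Predictors | f² | R² | AUC (p = 0.50 to 0.10) | Sensitivity at 80% specificity |
|---|---|---|---|---|
| 10 | 0.0852 | 0.078 | 0.66 to 0.75 | 40% to 55% |
| 20 | 0.114 | 0.102 | 0.68 to 0.79 | 43% to 61% |

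One and the same R² (0.038) goes with an AUC of 0.61 or 0.68 depending on how many people decline. R-squared therefore does not even fix the discrimination.

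**4. Optimism of in-sample R-squared**

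For k predictors unrelated to the outcome, the expected R-squared in an ordinary least squares fit is k/(N − 1). With N = 200 this is 10/199 = 0.05 for 10 predictors and 20/199 = 0.10 for 20. The second value is about as large as the true R² (0.102) detectable with 20 predictors. This is before any selection; choosing the best few of a larger pool adds to it. An adjusted R-squared corrects for the predictors fitted, but not for those tried and dropped.

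**The case against.** The strongest reply has four parts.

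- **Classification is planned.** A reader might infer that the article has no method for classifying individuals. That is wrong, because k-nearest neighbours is one. It is offered as an alternative, however. The final predictors are chosen elsewhere by R-squared, and nothing says how the classifier will be judged.
- **Accuracy measures belong in the analysis plan.** This is a condensed article, and cross-validation and AUC are details it may leave to a document not shown. This stands as far as missing detail goes, and the article does not say that accuracy will go unreported. What remains is that the article does fix a selection criterion, and that criterion does not suit the stated aim.
- **The research question is about predictors.** Study aims first asks which variables predict transition, and the Abstract and Conclusion speak of possible predictors. A reader might infer that the authors will call any significant set a validated tool; the text does not say so. But the same section states an instrument as the objective, so the mismatch remains.
- **The AUC figures are not the article's.** This is correct. A reader might infer that the tool will reach an AUC of only 0.6 to 0.7. That holds for one marker at the smallest effect detectable with 80% power. The product is a combination of markers, and over the assumptions tried, from d = 0.2 to f² = 0.15, the range is about 0.56 to 0.82. Nor would such a marker misclassify most people. At 80% specificity and 15% decliners, 0.15 × 0.388 + 0.85 × 0.80 = 74% are classified correctly. It misses most decliners, which is a different statement.

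**Conclusion.** The point holds as a mismatch between aim and criterion. The article sets out to build an instrument that detects a categorical outcome in individuals. It then selects predictors by R-squared and reports hazard ratios, and neither quantifies classification. Its one classifier has no stated accuracy measure, and in-sample R-squared after selection among many markers in about 200 people is optimistic. This part rests on the text alone.

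The size is illustrative. If the sized effect is a single predictor with f² of about 0.04, a marker of that size has an AUC of about 0.61 (50% decliners) to 0.68 (10%) and finds 33–43% of decliners at 80% specificity. A joint test of 10–20 predictors corresponds to about 0.66 to 0.79. These values depend on the assumed test, number of predictors, decline rate and binormal model. They show that being detectable at the planned power does not establish screening value. They do not show that the finished instrument will discriminate poorly.

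**What to change.** State in the analysis plan that the regression-based instrument and the k-nearest-neighbours classifier are both judged by cross-validated AUC, by sensitivity and specificity, and by predictive values at the observed decline rate, each with an interval. Repeat marker selection and the choice of k inside every fold, so that the estimates include the cost of selection. Keep R-squared and hazard ratios as descriptive results, and base any screening-tool claim on the accuracy estimates.

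A go/no-go bound on the AUC, or one particular fixed specificity, would be a matter of preference and is not needed for this correction.

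The cost is analysis-plan wording and a little more computing, with no new data or visits. The downside is a headline figure that will probably be less favourable than the in-sample one.

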## Data Availability

All participant information and data will be stored securely and identified by a coded ID number only to maintain participants’ confidentiality. Data can be obtained from the corresponding author upon reasonable request.

## Abbreviations

ADL: Activities of daily living
CERAD-Plus: Consortium to Establish a Registry for Alzheimer’s Disease
CHI: Cognitively healthy individuals
FLei: Fragebogen zur geistigen Leistungsfähigkeit
MCI: Mild cognitive impairment
MoCA: Montreal Cognitive Assessment
OA: Older adults
SCI: Subjective cognitive impairment
SENDA: Sensor-based systems for early detection of dementia
SST: Serial Sevens Test
VFT: Verbal Fluency Test
